#### Site visits to evaluate traffic infrastructure

By conducting standardised site visits and observations (based on Schnell et al. [33]), we aim to assess neighbourhood conditions for active mobility. Site visits will serve to develop a comprehensive understanding of the study area and its spatial as well as social characteristics [34]. They integrate various techniques, such as observation and mapping, and are particularly well suited or identifying local conditions in a structured manner. Two trained members of the project team – one familiar with the area and one without prior local knowledge – will carry out the observations to ensure diverse perspectives. The observers will document selected aspects such as infrastructure quality, spatial experience, environmental factors, safety, and accessibility using structured notes, photographs, and maps.

#### Air quality measurement

We will conduct exploratory measurements of particulate matter (PM2.5 and PM10) concentrations in all six study areas [35]. Data collection will begin in the first project year and continue at regular intervals until the conclusion of the project. Currently, only data from official monitoring stations along major roads are available, which provides limited insights into air quality variation within neighbourhoods. In each neighbourhood, three measurement sites – representing low, medium, and high expected pollution levels – will be identified using a Geographic Information System (GIS). This approach enables the analysis of spatial factors such as population density, land use, and traffic intensity. Measurements will be carried out using Senseboxes [36], low-cost sensors that record particulate matter in real time. Observers will document PM concentrations along with GPS coordinates, measurement time, wind speed, and key site characteristics, including proximity to roads or green spaces. To maximise comparability, the short-term measurements will be conducted on weekdays under similar weather conditions.

### Secondary data sources

In addition to primary data, we will collect secondary data from various sources provided by the respective city authorities. These data will include information on the population structure of the study areas (e.g. number of inhabitants, age distribution, proportion of residents with a migration background, unemployment rates, and other sociodemographic indicators), as well as aggregated health and environmental data. Health data will include indicators such as life expectancy, results from school entry examinations, and other aggregated public health statistics. Environmental data will include information on air and noise pollution, heat exposure, and the availability and quality of green spaces.

For the intervention areas, we will also gather detailed information on the IUDPs’ implementation processes from the responsible authorities, including data on expenditures, participation rates, and the use of specific interventions such as counselling services or small subsidy programmes for private homeowners. Additionally, we will document any delays in the implementation and their underlying causes. To ensure a longitudinal perspective, secondary data will be collected retrospectively for a period of ten years prior to the start of the respective IUDP and continuously throughout the project duration.

In the control areas, we will assess whether any interventions are planned or implemented that target similar dimensions as the IUDPs but have not been formally developed or approved as such. Close cooperation with local authorities and the wider network of practitioners in the study areas, established during the project conception phase, will ensure comprehensive and reliable access to these data sources.

### Eligibility criteria

To participate in primary data collection activities, residents must be at least 18 years old, and their main residence must be within the respective study area. For the focus groups, we will consider including residents aged 16 and older to capture the perspectives of younger population groups.

### Recruitment of the participants

For the surveys, contact details of potential participants will be provided by the local residents' registration office. These contact details will be stored in a secure database on a server at the University of Bremen. We will send an invitation letter to all potential participants, which includes study information and an individual code to access the online survey. Informed consent will be obtained immediately before the survey begins.

At the end of the survey, participants will be asked whether they are interested in taking part in an additional assessment using accelerometers to measure physical activity and sleep. The accelerometer assessment will be described and an info sheet with more details will be attached for download. Interested individuals can contact the study team via a dedicated phone number or email address to receive further information and to schedule the assessment period. During an in-person appointment at the participant’s home, written informed consent will be obtained, and the accelerometers will be handed out.

For the interviews with stakeholders, the focus groups with residents, and further participatory formats, participants will be recruited through personal contact facilitated by cooperating stakeholders.

Throughout the entire project duration, we will engage in promotional activities for both the overall project and for specific data collections (such as surveys or interviews) to support recruitment and increase public awareness of the project. For these purposes, a project website and various social media accounts have been created. Face-to-face engagement and dialogue will also be supported through participation in local events, such as health promotion days, summer fairs, family festivals, neighbourhood council meetings, and local working group sessions related to urban development. In addition, we contacted local newspapers to publish tailored information about the project and the data collections relevant to each study area.

### Allocation

The allocation to either an intervention area or a control area is defined by the participants’ main residence.

### Interventions

The IUDPs comprise a broad variety of interventions. In the following, we describe the different interventions of the respective IUDP.

#### IUDP 1 (Bremen)

In Bremen Blumenthal, the IUDP was launched in 2023 with the aim of revitalising the historic district and creating healthier, more equitable living environments. The programme combines spatial, social, and physical environmental interventions to address long-standing challenges of structural inequality and urban neglect.

A significant contextual development is the construction of a new vocational training campus on the site of the former local wool factory, a large-scale industrial brownfield site. While formally not part of the IUDP, the campus is expected to attract thousands of students and professionals, offering new opportunities for education and employment as well as reshaping the district’s social and economic dynamics. The IUDP builds on this transformation by ensuring that the campus is well integrated into local life – for example through new pedestrian links to the district centre and measures that facilitate broad and inclusive access to its opportunities.

Complementary interventions within the IUDP focus on strengthening the social and cultural infrastructure of the historic centre. The former town hall will be renovated and repurposed as a multifunctional neighbourhood hub, hosting a library, community spaces, and social services to provide low-threshold access to resources and support. The surrounding market square, adjacent streets, and a large public green space will be redesigned to become more attractive, accessible, and inclusive areas for recreation and encounter, encouraging greater use by diverse groups of residents.

To counter widespread vacancy and housing neglect, the programme supports property owners with funding for renovations, energy-efficient upgrades, and heritage-sensitive restoration. In addition, the municipality has acquired several dilapidated housing units for renovation and reallocation as socially managed housing. These measures aim to ensure decent living conditions, reduce housing-related health risks, and prevent segregation and displacement.

The IUDP integrates a broad range of climate mitigation and adaptation measures. By preserving and upgrading existing buildings, the programme aims to retain “grey energy” while improving energy efficiency and exploring alternative energy systems. Renovations will favour low-carbon materials where possible, while adaptation strategies include minimising surface sealing, promoting nature-based rainwater management, and introducing green roofs or façades. Further elements such as shading contribute to urban cooling, reduced heat stress, and improved well-being. Collectively, these measures are expected to contribute to the creation of healthy, climate-resilient, and accessible living environments for diverse members of the community reflecting an integrated approach to urban sustainability.

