**Methods:**

We will compare three IUDP intervention areas with three control areas in the respective cities using a mixed-methods design. Quantitative and qualitative data will be collected to assess both process and outcome quality of the IUDPs. Primary data collections include resident surveys and focus groups, qualitative interviews with stakeholders, as well as environmental and infrastructural assessments, including air-quality measurements, site visits, and observations related to active mobility and urban green spaces. Secondary data on population structure, aggregated health indicators, and local implementation processes will be provided by the municipalities. Analyses will follow a difference-in-differences approach to identify changes attributable to IUDP implementation while accounting for similar developments in the control areas.

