#### Surveys of the residents

We will conduct two surveys in the study areas, one in the first and the other in the third year of the project. The surveys will target residents aged 18 years and older living within the defined study areas. In Bremen and Wuppertal, all residents will receive a personal access code enabling them to complete the survey online. In Wattenscheid-Mitte, due to the substantially larger population, a random sample of residents will be invited to participate, with the number of invitations adjusted to achieve a sample size comparable to the other intervention areas. The survey will be implemented on LimeSurvey, an open-source online survey tool [19]. The survey will include a set of validated questionnaires: Warwick Edinburgh mental well-being scale [20], Short Scale Measuring Perceived Social Participation [21], Oslo-3-Items-Social-Support Scale [22], self-efficacy short scale [23], and Abbreviated Place Attachment Scale (APAS) [24]. We will also use items on general mental and physical health status from the German Federal Health Reporting surveys, provided by the Robert Koch Institute (RKI) [25]. Furthermore, we will collect information about the participants’ living and housing situation, their subjective assessment of their living environment concerning (1) traffic infrastructure, (2) impairments due to noise, air pollution, and other environmental threads, (3) the proximity and accessibility of public green spaces, as well as their perceived impact on and involvement in urban planning decisions affecting their living environment. We will provide translations of the questionnaire in the most common languages of the study areas.

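### Bremen: a large campus outside the IUDP sits in the intervention area, so the I1–C1 difference-in-differences estimates IUDP plus campus, not the IUDP alone

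*Protocol article*

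**What the plan says.** The article's section on IUDP 1 (Bremen) introduces the campus: "A significant contextual development is the construction of a new vocational training campus on the site of the former local wool factory". It continues: "While formally not part of the IUDP, the campus is expected to attract thousands of students and professionals". The same sentence expects new education and job opportunities and a change in the district's social and economic life. The plan is then tied to the campus: "The IUDP builds on this transformation by ensuring that the campus is well integrated into local life".

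The abstract (Methods) states what the analysis is for: "Analyses will follow a difference-in-differences approach to identify changes attributable to IUDP implementation while accounting for similar developments in the control areas". Data analyses applies DiD to the survey, environmental and secondary quantitative data. It also mentions multivariate analyses and stratification by social indicators, without naming covariates.

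On the survey: "We will conduct two surveys in the study areas, one in the first and the other in the third year of the project". Primary data collection methods calls both surveys cross-sectional. On exposure: "The allocation to either an intervention area or a control area is defined by the participants’ main residence". Eligibility criteria requires age 18 or over and main residence in the area; no length of residence is stated.

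On concurrent developments, Secondary data sources and the Discussion both commit to tracking IUDP-like activity in the control areas. Neither makes the same commitment for non-IUDP developments in the intervention areas. The Discussion lists retention, implementation delays and control-area developments as challenges, and omits this one.

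**The concern.** For the I1–C1 contrast to be read as the IUDP effect, I1 and C1 must have moved in parallel apart from the IUDP. The article itself names a large development in I1, places it outside the IUDP, and expects it to change the district. Nothing in the design or the stated safeguards separates the two.

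Bremen carries results that the other cities cannot replace. It is the only city assigned Outcomes I (Data analyses) and the only one with accelerometry (Accelerometery). It also has the most recently launched IUDP: its first measures date from the end of 2023, against 2015 in Bochum and 2007 in Wuppertal. If the campus improves or worsens employment, amenities, traffic or well-being in Blumenthal, that change will be reported as something the IUDP did.

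**Working it through.** The article states no effect size or power figure on this point, so there is nothing to reproduce. The check is on what the contrast identifies.

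**Step 1. What the DiD estimates.** Let τ be the IUDP effect. Let γ be the campus effect on existing I1 residents between the two measurements, including any interaction with the IUDP measures that link the campus to the district. Let s be the share of I1 adults at wave 2 who moved in because of the campus, and d their outcome gap from existing residents in SD units. With no such development in C1:

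E[DiD, I1–C1] = τ + γ + s·d

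Only τ matches the abstract's attribution wording.

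**Step 2. Do the stated safeguards remove γ?**
- Subtracting C1 does not. It removes shared change, no campus is described for C1, and the Discussion says control areas do not directly adjoin the intervention areas.
- Monitoring control areas does not. It detects contamination of C1, whereas this development is in I1.
- Covariate adjustment does not. An area-wide campus effect coincides with the I1-by-time term. Adjustment can reduce measured differences in who answers, which bears on s·d only.

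**Step 3. Illustration of γ (assumed value).** With τ = 0, γ = 0.10 SD and no in-movers: DiD = 0 + 0.10 + 0 = 0.10 SD, all of it credited to the IUDP.

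**Step 4. Illustration of s·d (conditional on in-migration).** From Table 1, I1 has 10,706 residents, 23.6% of them under 18. Adults = 10,706 × (1 − 0.236) ≈ 8,179. For M adult in-movers before wave 2, s = M / (8,179 + M). M and d are assumptions.

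| M | s | s·d at d = 0.2 | at d = 0.3 | at d = 0.5 |
|---|---|---|---|---|
| 0 | 0% | 0 | 0 | 0 |
| 250 | 3.0% | 0.006 | 0.009 | 0.015 |
| 500 | 5.8% | 0.012 | 0.017 | 0.029 |
| 1,000 | 10.9% | 0.022 | 0.033 | 0.054 |
| 2,000 | 19.6% | 0.039 | 0.059 | 0.098 |

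With M = 0 this term vanishes and γ remains. With τ = 0, γ = 0.10, M = 1,000 and d = 0.3: DiD = 0 + 0.10 + 0.109 × 0.3 = 0.133 SD.

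**Step 5. Timing.** The article gives no campus opening date. For survey and accelerometer data, γ counts only so far as the campus acts between project years 1 and 3. The secondary series runs from ten years before the IUDP to the end of the project, so campus effects at any time in the IUDP period enter it.

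**The case against.** **The campus could be treated as part of the IUDP package.** The Background says IUDPs set off further activities under separate funding. This does not answer the point: the Bremen section puts the campus formally outside the IUDP and describes the IUDP as building on it, which is the reverse direction.

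**A reader might infer that thousands of new residents will enter the I1 survey sample and shift its mean.** The documents do not support that. They say the campus will draw students and professionals, not that these people will live in Blumenthal. Commuters fall outside the survey because eligibility rests on main residence. With no opening date, it is not shown that anyone moves in before wave 2. The composition term is a possibility of unknown size, and this part of the objection stands.

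**A reader might also infer that the campus affects I1 alone.** That rests on its location and on the absence of a described counterpart in C1. Its education and jobs need not be confined to Blumenthal residents, and some benefit could reach C1. Equal effects in both areas are not plausible on the article's own description, but the exact difference is unknown.

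**Restricting the main analysis to people already resident at wave 1 looks attractive.** It would not work as the lead analysis. The surveys are cross-sectional with no linkage described, so wave 1 would still contain later leavers while wave 2 held only stayers. Staying may itself be an effect of the IUDP, which seeks to reduce vacancy. And γ would remain.

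**Covariates, analysis sets and questionnaire items may be fixed in documents not shown.** That is fair, and length of residence may already be asked under living and housing situation. But the attribution wording and the control-only monitoring are stated in this article, and a later analysis plan cannot separate γ from τ with these data.

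**Conclusion.** The point holds as a limit on attribution in one city. To the extent that the campus takes effect between the measurements, the I1–C1 DiD estimates the joint effect of IUDP and campus, for survey, accelerometer and secondary-data results alike. The abstract's claim of change attributable to IUDP implementation is not supported for Bremen as worded.

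The conclusion rests on three things: the article's own description of the campus as outside the IUDP and expected to change the district; the absence of a described equivalent in C1; and some campus effect falling within the measurement window. The first two are in the text, the third is an assumption. The size is unknown. Every figure above beyond the Table 1 inputs is illustrative. Compositional bias from in-migration is conditional on something the documents do not say. No campus is described for Bochum or Wuppertal, so the point does not extend to them.

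**What to change.** 1. State the Bremen estimand as the effect of the IUDP together with the campus, and word attribution to match for Bremen survey, accelerometer and secondary-data results.
2. Extend the monitoring of non-IUDP developments from the control areas to the intervention areas. Record campus milestones (construction stages, opening, numbers of students and staff) against the dates of the two waves.
3. In I1 and C1, at both waves, ask length of residence and campus affiliation, if the questionnaire does not already do so.
4. Prespecify a sensitivity analysis in longer-term residents, using the same residence-duration cut-off at each wave. A cut-off at least as long as the gap between waves ensures that those kept at wave 2 were already resident at wave 1. Keep all residents as the lead analysis. This analysis speaks to composition only and does not isolate the IUDP from the campus.

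The cost is one or two short survey items, some added documentation, and a narrower claim for Bremen.

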#### IUDP 2 (Bochum)

In Bochum Wattenscheid-Mitte, the IUDP was launched in 2015 with the aim of revitalising the inner-city area of Wattenscheid, a former independent city that became part of Bochum following local government reorganisation in 1975. Wattenscheid was shaped by an active coal mining industry until the mid-1970s and due to structural economic changes is characterised today by a comparatively disadvantaged population. Children in particular show poorer health outcomes at school entry examinations than in other districts of the city, including higher rates of overweight, lower motor skills, and more frequent hearing impairments.

The overall objective of the IUDP is to create a healthier and more family-friendly neighbourhood. The programme combines spatial, social, and physical environmental interventions to address long-standing structural inequalities, with a particular focus on deficits in urban planning and the built environment. Since 2015, several renewal interventions have been completed, including the redesign of parks such as the Friedenspark am Ehrenmal and the Stadtgarten, which now offer diverse functions for play, recreation, and culture. The redesign of Monte-Schlacko – a park located on a former mine dump – is currently underway. Another example of ongoing spatial transformation is the conversion of a former sports field into a multifunctional space for wheel-based active mobility, complemented by tree planting and a rainwater retention basin as part of climate adaptation strategies.

Other interventions include the redesign of playgrounds and schoolyards, as well as the redevelopment of the central square. While the square is both the neighbourhood’s main public transport hub and heavily sealed, making it a recognised heat hotspot in summer, it has long been perceived as lacking comfort and urban quality. Its redevelopment therefore aims to improve both usability and climate resilience, creating a more attractive and comfortable public space for residents. Complementary schemes such as façade improvement grants encourage private investment in the upgrading of residential buildings.

Community funding within the IUDP framework supports a wide range of social and health-related projects. For instance, the annual Health Weeks held each spring provide health-related activities for residents and facilitate networking among local stakeholders.

In line with the guiding principle of health and family, considerable efforts are made to promote health besides improving the built environment. For more than ten years, the local neighbourhood management has been building a health network that connects different actors in health promotion and healthcare. One major achievement is the opening of a Community Health Centre (“health kiosk”) in spring 2025, after years of preparation. The centre aims to guide diverse communities through the German health system, improve health literacy, and support the development of new health services. It is co-financed by a health insurance fund and the City of Bochum, operated by a dedicated company that includes a local charity organisation.

The IUDP also acts as a platform to mobilise additional resources and partnerships. Between 2020 and 2024, a joint project of the city’s planning and health departments, neighbourhood management, a health insurance fund, and a local university promoted physical activity on redesigned public sites and developed tailored outreach activities for groups that are often hard to reach. Among these, a cycling course for migrant women offered by the Bochum city sports association illustrates how targeted, low-threshold offers can contribute to social inclusion and health promotion at the neighbourhood level.

